#### 2.7.2. Statistical Analysis

A longitudinal mixed-effects statistical model (also referred to as hierarchical or multilevel modeling) will be used to analyze the overlap between baseline to post-intervention for all outcome measures [81], provided that the data allows for such an analysis. A mixed-effects model can account for individual differences through the inclusion of random effects and is known to have increased statistical power by its ability to use all available data points.

### 2.8. Blinding

Neither the participants nor the principal investigator will be blinded to baseline period allocation. Due to the nature of the intervention, the clinician (principal investigator) will not be blinded to the intervention. Statistical analyses will be conducted by an independent statistician.

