### 2.4. Participant Evaluation

Before the clinical examination procedures begin, eligible patients based on pre-screening criteria, must sign the informed consent form indicating their willingness to participate in the study. Once signed, all participants will first undergo a comprehensive subjective history followed by various clinical examination tests to determine full eligibility, which will all be completed by the principal investigator who is a licensed Physical Therapist with board certification as an Orthopedic Clinical Specialist with over 15 years of clinical experience. All participants will undergo a manual examination for TrPs in the posterior cervical muscles using diagnostic criteria supported by expert consensus [39]. Through palpation, TrPs will be identified by the presence of a hypersensitive spot in a taut band of skeletal muscle and referred pain or sensation upon stimulation [40]. A recent systematic review reported uncertainty with recommending TrPs as an entity in the clinical examination of patients with migraine, yet TrPs were frequently assessed in the included studies, and the recommendations were limited only by study heterogeneity and inadequate results reporting [41]. Stimulation to TrP areas will be performed to reproduce any symptom experienced by the patient, either partially or completely, whereby the symptom is recognized as a familiar experience by that patient. i.e., in this case, reproduction of migraine attack symptomatology [13,18,39]. In addition, the pressure pain thresholds (PPTs) will be assessed in the location of the TrPs using an analogue algometer (Force Dial FDK 20, Wagner Instruments, Greenwich. Connecticut), which has shown good concurrent validity in patients with migraine [42]. Patients with migraine headache show decreased PPT levels over local areas in the cervical musculature [43], including the suboccipital muscles [44].

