### 2.5. Interventions

During the intervention phase, patients will receive five sessions of dry needling with IMES, one session per week for five weeks total during the intervention phase. Dry needling will be delivered by a Physical Therapist (principal investigator) who has over 10 years of clinical dry needling experience and is certified by a course program that provides 80 h of dry needling instruction. Sterilized disposable stainless-steel needles will be used and will include one standard size, 0.30 mm × 50 mm APS needles (Agupunt, Barcelona, Spain). Dry needling will be applied to TrPs in at least two of the following posterior cervical muscles: splenius capitis, splenius cervicis, semispinalis capitis/cervicis, cervical multifidi (from C2–4), and obliquus capitis inferior. These muscles were chosen because they receive innervation from the upper cervical dorsal rami and therefore may influence the TCC. Trigger points will be treated on the side of the headache or bilaterally if they are present. For the posterior cervical muscles, they will be treated as one muscle group with all needling to be performed posterior to the transverse processes and lateral to the spinous processes of C2 to C6. A medial–caudal–ventral approach will be used, progressively treating deeper toward the lamina of the caudal vertebrae while monitoring for reproduction of symptoms (local or referred pain or sensation) and for a local twitch response (LTR). A LTR is characterized by a contraction of part of the taut band when needling a sensitive area within a TrP and is often used clinically to confirm the needle has reached a trigger point [58,59]. Since deeper muscles in the posterior cervical region are inaccessible to palpation, the LTR will be used as an objective sign of the TrP location. For the suboccipital muscles, only the obliquus capitis inferior will be needled as it is the only one that can be safely needled due to the proximity of the vertebral artery above the posterior arch of the atlas and the foramen magnum. With the patient in the prone position, the needle will be inserted inferiorly and laterally to the target TrP between the transverse process of C1 and the spinous process of C2, in the medial half of the muscle towards the posterior arch of C1 using a cranial-medial technique to direct the needle towards the patient’s opposite eye (Figure 2) [60,61].

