### 2.6. Outcome Measures

#### 2.6.1. Primary Outcome Measure

For this study, the reduction in headache frequency, which is the reduction in the number of headache days over a one-month period, will be the primary outcome measure [71]. The primary end point for this study is the 6th, and final, visit at the end of the intervention phase where the change in the headache frequency will be assessed. Headache diary reports will be sent to the principal investigator each week during the baseline and intervention periods of the study. The headache diary reports will be sent through a secure electronic patient portal as a PDF report generated through the Migraine Buddy smartphone application. Use of this application for research purposes has increased in recent years to capture headache data and for outcome monitoring [72,73]. Headache characteristics, triggers, and medication use will also be recorded in the headache diary with a time stamp feature for data collection in real time. All headache diary data will be analyzed and stored on a Microsoft Excel spreadsheet, with all participant information de-identified. A migraine day will be defined as a day with a headache that lasts at least 4 h, which meets the International Classification of Headache Disorders 3rd edition criteria for migraine without aura, migraine with aura, and probable migraine, or a day with a headache that is successfully treated with migraine-specific acute medication [36].

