### 2.7. Data Analysis

#### 2.7.1. Visual Analysis

In this SCED study, the primary and secondary outcome measures will be analyzed separately using both visual and statistical analyses. First, we will conduct an exploratory data analysis to observe within- and between-phase patterns in the data with emphasis on level (mean score for the data), trend (slope), variability (spread of data points), and overlap (calculation of points overlapping between phases) [29,31,78]. The stability of data points will be assessed following the completion of the baseline phase [78]. Individual participant data will be represented using data visualization methods, including a graphical plot for each outcome variable both within and across participants. Non-overlap indices will be used to further assess overlap and will include non-overlap of all pairs (NAP) or the baseline-corrected Tau-U, depending on the baseline trend [79]. In addition, NAP, or baseline-corrected Tau-U will be used to measure effect size [31,80].

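### The randomised baseline length is disclosed to participants and investigator without a stated reason, although the start date could be withheld for most of the baseline

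*Protocol article*

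**What the plan says.** Section 2.8 of the protocol article states: "Neither the participants nor the principal investigator will be blinded to baseline period allocation". The next sentence reads: "Due to the nature of the intervention, the clinician (principal investigator) will not be blinded to the intervention". That reason concerns the clinician and the needling. No reason is given for opening the baseline tier to either party. The section closes with: "Statistical analyses will be conducted by an independent statistician".

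Section 2.1 sets four tiers of 4, 5, 6 and 7 weeks of baseline, each followed by 5 weeks of treatment, and presents random assignment to a tier as the step that supports internal validity. Enrolment is non-concurrent, and each participant serves as their own control.

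Section 2.6.1 makes the reduction in headache days over one month the primary outcome, taken from a smartphone diary that the participant completes. It adds: "Headache diary reports will be sent to the principal investigator each week during the baseline and intervention periods of the study". According to Section 2.5, the same investigator delivers the needling.

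Section 3.2 discloses that participants and investigator are unblinded throughout. It concedes that this can exaggerate the apparent benefit of dry needling, and it notes that assessor blinding is recommended for this type of design.

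**The concern.** Two kinds of knowledge are left open under one heading. Knowledge of the needling is unavoidable. Advance knowledge of the start date is not, because nothing in the delivery of the treatment requires a participant to know the date several weeks before it.

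The distinction matters because the staggered random start stands in for a control arm. It helps to separate a treatment effect from a time effect because the switch occurs at a point that chance has set. If the participant knows that point in advance, the weeks just before it can be affected by knowing it. The participant may record more fully, hold back or increase acute medication, or change daily habits as the date approaches. The outcome is self-reported, so a change in reporting passes straight into the count. Acute drug use can also matter directly: under the migraine-day definition in Section 2.6.1, a headache that responds to migraine-specific acute medication qualifies.

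A shift in the last baseline weeks changes the reference level for the primary comparison. If the shift is upwards, part of the later fall is spurious. If it is downwards, part of a real fall is hidden.

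**Working it through.** **Plan's own figure.** Section 2.1 gives a total duration of 9 to 12 weeks. Baseline plus 5 weeks: 4 + 5 = 9, 5 + 5 = 10, 6 + 5 = 11, 7 + 5 = 12. The figure reproduces. The baseline lengths are 28, 35, 42 and 49 days.

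**Inputs.** Baseline lengths come from Section 2.1. The entry minimum of 15 headache days per month comes from Section 2.3.1. The documents give no figure for anticipation, so the following are assumptions:
- The participant learns the tier at allocation.
- One extra headache day is reported in each affected week, and the direction is upwards.
- The baseline rate is averaged over the whole tier.

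**Formula.** Shift per 28 days = (extra days ÷ baseline days) × 28.

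| Tier | Baseline days | Two affected weeks (open date) | One affected week (one week's notice) |
|---|---|---|---|
| 1 | 28 | 2/28 × 28 = 2.0 | 1/28 × 28 = 1.0 |
| 2 | 35 | 2/35 × 28 = 1.6 | 1/35 × 28 = 0.8 |
| 3 | 42 | 2/42 × 28 = 1.3 | 1/42 × 28 = 0.7 |
| 4 | 49 | 2/49 × 28 = 1.1 | 1/49 × 28 = 0.6 |

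Against 15 days, the open-date shift is 2.0/15 = 13% in tier 1 and 1.14/15 = 8% in tier 4. With one week's notice it is 1.0/15 = 7% and 0.57/15 = 4%. If the one-month baseline were instead the last 28 days before the switch, the shift would be 2.0 (open) or 1.0 (one week's notice) in every tier.

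**Limit of the one-week column.** In tier 4 a participant who knows both the 4-to-7-week range and the length of notice can work out the date. With one week's notice, tier 3 would be announced at the end of week 5. No announcement then means a start after week 7, so two weeks of anticipation return and the tier 4 figure goes back to 1.1.

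**What concealment cannot reach.** A simulation with no treatment effect, 15 headache days per 28 and weekly binomial counts gave a mean NAP of about 0.51 with no reporting change. With a purely expectancy-driven fall of 2 days per 28 during treatment it gave about 0.60 (null value 0.50). This shows that the index responds to reporting bias. It says nothing about a gain from concealing the tier, because expectancy during treatment would be unaffected.

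**The case against.** The case on the other side is substantial.

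- **The limitation is already disclosed.** Section 3.2 admits the lack of blinding and its likely direction. That stands, but the section treats blinding as a whole and does not explain why the start date must be known early.
- **The bias is not shown to occur.** Its size and direction are assumed. That stands, and the point is therefore about a risk.
- **Other safeguards exist.** Section 2.7.1 assesses baseline stability and uses baseline-corrected Tau-U where there is a trend. NAP, Tau-U and the mixed model are computed, so no reader's judgement enters those calculations. All of this is correct, but a calculation cannot remove a reporting change already in the diary. A late rise in reported days is itself a baseline trend, and correcting for it can enlarge the apparent fall.
- **The remedy is partial and recruitment is under way.** Both stand. With four participants, some may be under open and others under concealed allocation. If each tier is used exactly once, which the documents do not say, the investigator would also know the last participant's tier by elimination.

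A reader might go further and infer that the unblinded investigator reads the diary data with phases visible, since Section 2.7.1 says "we will conduct an exploratory data analysis to observe within- and between-phase patterns in the data" and Section 2.8 assigns only the statistical analyses to the independent statistician. The documents do not support this. The pronoun names no reader, whether the statistician is masked is not described, and a condensed article may leave such detail out. Nor would hiding the phase line help. The planned reading needs the phase boundary, and because treatment always fills the last 5 weeks, the series length gives the tier away.

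A reader might also infer that a known tier could influence the eligibility decision, because the investigator carries out that examination (Section 2.4). No section says that the tier is known before eligibility is settled.

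**Conclusion.** The point holds in a limited form. Section 2.8 makes a decision that opens the baseline tier to both parties and gives no reason for it. With a self-reported primary outcome and no control arm, advance knowledge of the start date can bias the baseline-to-treatment contrast, and most of that knowledge could be withheld at little cost.

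Under the stated assumption of one extra reported day per affected week, the open date shifts the baseline by 1.1 to 2.0 days per 28 across tiers. One week's notice brings this to 0.6 to 1.0, unless a tier 4 participant deduces the date. These figures illustrate sensitivity and are not estimates, because the documents contain no data on anticipation. The weakness does not invalidate the trial, and the change would not make it a blinded one.

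**What to change.** Amend Section 2.8, for participants not yet allocated, as follows:

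1. Someone other than the treating investigator holds the allocation. The independent statistician already engaged is one option, although the article gives that person no such role at present.
2. Participants are told only that treatment starts after 4 to 7 weeks. The length of the notice period is best left unstated to them, which makes the longest tier harder to deduce.
3. Participant and investigator learn the date about one week ahead.

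Baseline lengths and the treatment plan stay as they are. Section 3.2 should then say what remains: anticipation in the last baseline week, deduction of the longest tier, and expectancy once needling begins. The report should state which participants were under open and which under concealed allocation.

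The cost is an amendment to the wording, including what participants are told, a small task for the allocation holder, and first treatment visits booked at about one week's notice. Participants already allocated stay under open allocation. Because recruitment is active, the change is worth less with each further participant allocated.

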### 2.9. Adverse Events and Monitoring

Monitoring for adverse events (AEs) will be performed at each treatment visit by the principal investigator and will be recorded on the participants’ behalf using the headache diary. Participants will be given an informative handout describing what steps to take in the event of an adverse reaction to dry needling, and participants will be advised to immediately seek medical attention and notify the principal investigator and their physician. Possible minor side effects of dry needling may include temporary pain during needling, numbness or tingling, minor bleeding, bruising, drowsiness, tiredness, dizziness, and possible fainting [82]. More significant adverse events include pneumothorax and cervical epidural hematoma [83,84]. However, none of the muscles selected for treatment in this study are in proximity to the lung field. If a subject demonstrates an increase in the average headache pain intensity of more than two points on the NPRS following the first week of treatment or if a subject reports an increased number of consecutive headache days above their reported weekly average, the principal investigator will consult the patient and recommend discontinuation of the study.

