## Abstract

*Background and Objectives:* Trigger points (TrPs) are prevalent in patients with migraine headaches. Needling interventions targeting TrPs in migraine patients may reduce the intensity and frequency of headaches, yet systematic reviews reveal a lack of robust evidence. Intramuscular electrical stimulation (IMES) is a modality that delivers electrical current into muscles and TrPs, with recent studies suggesting it may amplify the therapeutic effects of dry needling peripherally and centrally. This could be advantageous for patients with migraine and symptomatic TrPs. *Materials and Methods:* This study will implement a multiple baseline single-case experimental design (SCED). In a clinical setting, a SCED study lends itself to conducting research with only a few patients that each serve as their own controls. In this SCED study, four participants with chronic migraine will be enrolled in a non-concurrent manner and randomized to one of four baseline measurement periods (4, 5, 6 or 7 weeks), leading to four potentially different start dates for each participant in the intervention phase. During the intervention phase, patients will receive five sessions of dry needling with IMES, one session per week for five weeks. The primary outcome measure will be headache frequency, i.e., the reduction in the number of headache days over a one-month period using electronic headache diary data from the Migraine Buddy smartphone application. Secondary outcome measures will be changes in mean migraine pain intensity using a numeric pain rating scale (NPRS), migraine disability using the Migraine Disability Assessment Test (MIDAS), the Headache Impact Test (HIT-6), and changes in selected cervical musculoskeletal impairments including pressure pain thresholds (PPTs) over TrPs, the craniocervical flexion test (CCFT), and cervical active range of motion (AROM). Primary and secondary outcome measures will be analyzed separately using both visual and statistical analyses. *Results*: Actively recruiting participants. This project was approved by the Mass General Brigham Institutional Review Board (protocol #2023P000931) and is registered with ClinicalTrials.gov (NCT05893914). *Conclusions*: This study will seek to determine the effects of a five-week intervention period of IMES to TrPs in the posterior cervical muscles of subjects with chronic migraine.

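### Adverse events are recorded in the primary-outcome diary by the unblinded treating investigator, at treatment visits only, with no stated separation from headache entries and no baseline enquiry

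*Protocol article*

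**What the plan says.** Section 2.9 (Adverse Events and Monitoring) fixes who looks for AEs, when, and where they are written down. "Monitoring for adverse events (AEs) will be performed at each treatment visit by the principal investigator", and the events "will be recorded on the participants’ behalf using the headache diary". The minor reactions it expects are "temporary pain during needling, numbness or tingling, minor bleeding, bruising, drowsiness, tiredness, dizziness, and possible fainting". Headache is not on that list. Participants are also told to notify the investigator themselves after an adverse reaction.

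Section 2.8 states that "the clinician (principal investigator) will not be blinded to the intervention", and Section 2.5 that the same person delivers the needling.

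The diary named in 2.9 is the primary-outcome instrument. The Abstract has headache frequency measured "using electronic headache diary data from the Migraine Buddy smartphone application". Section 2.6.1 adds that "Headache diary reports will be sent to the principal investigator each week during the baseline and intervention periods of the study", and that "Headache characteristics, triggers, and medication use will also be recorded in the headache diary with a time stamp feature".

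**The concern.** The inference in this trial is the contrast between baseline (phase A) and treatment (phase B) within each of four patients. Anything that makes the outcome record differ between phases, other than the treatment, threatens that contrast. Section 2.9 gives the diary an additional contributor in phase B only: the person who gives the treatment and knows the phase. The text does not say how an AE entry is marked or kept out of the headache data.

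There is also a safety question. Tiredness, drowsiness, dizziness and tingling are non-specific, and people with chronic migraine may plausibly have them without needling; the document does not say how often. If they are asked about only after needling starts, a phase-B report cannot be set against the same patient's background, although Section 1 presents patients serving as their own controls as the strength of the design.

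**Working it through.** The document gives no figure of its own on this point, so there is none to reproduce. The check sets the sections side by side and adds simple arithmetic.

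**1. AE enquiries by phase.** Section 2.1 gives baselines of 28, 35, 42 or 49 days, then five weekly sessions over 5 × 7 = 35 days. Section 2.9 ties AE monitoring to treatment visits. Enquiries described: 0 in phase A for every tier, 5 in phase B.

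**2. Does the day definition keep AE entries out of the count?** Section 2.6.1 says "A migraine day will be defined as a day with a headache that lasts at least 4 h" and meets diagnostic criteria, or one with a headache successfully treated with migraine-specific acute medication. An entry of dizziness or bruising meets neither condition. But this defines a migraine day. The primary outcome in the same section is the number of headache days, for which no minimum duration is given. The 4-hour threshold therefore does not clearly protect the variable being counted.

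**3. Size, if an AE entry were counted as a headache day.** The document does not say this happens; the figures show only what is exposed.
- One extra day in 35, rescaled to 28 days: 1 × 28/35 = 0.8 days per 28 days. This is a maximum per entry, because an entry on a day already counted adds nothing.
- One such entry at every session, each on an otherwise headache-free day: 5 × 0.8 = 4.0 days per 28 days.
- That ceiling is not realistic here. Section 2.3.1 requires headache on at least 15 days a month. Taking a 30-day month and session days unrelated to headache (both assumptions), a share 15/30 = 0.5 of session days would already be headache days. That leaves 5 × 0.5 = 2.5 extra days, or 2.5 × 0.8 = 2.0 per 28 days, and fewer in patients with more frequent headache.
- If AE entries are kept apart: 0.
- Direction: added phase-B headache days shrink the reduction from baseline, so they work against an apparent benefit.

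**4. Comparator for non-specific reactions.** Let p be the probability that a patient has such a symptom in a given week without treatment. With no treatment effect, the expected number of positive weekly enquiries in phase B is 5p, anywhere from 0 to 5. The document gives no p, and the plan collects nothing in phase A from which to estimate it. For bleeding, bruising and needling pain, p is zero before needling and no baseline is needed.

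**The case against.** The strongest reply is that Section 2.9 only says where AEs are noted. A reader might infer that the investigator's entries change the headache count, or that different people complete the outcome diary in the two phases. The text supports neither reading. Only AE entries are attributed to the investigator, nothing says that headache days are entered, edited or classified by anyone but the participant, and nothing says that an AE counts as a headache day. A reader might also take the symptom reproduction monitored during needling (Section 2.5) to mean that provoked head pain is logged as headache. That passage concerns the needling procedure and does not mention the diary.

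Other points also stand. Diary data are time-stamped and treatment visits are dated, so AE entries could often be told apart. Headache worsening does have a baseline, because the diary runs in both phases. Safety is not among the stated aims. Sections 2.8 and 3.2 disclose the lack of blinding. Participants have a second reporting route.

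The article condenses a fuller protocol, in which an AE form may exist. This carries less weight, because the article is not silent on the instrument: it names one, and it is the one that supplies the primary outcome. The disclosed lack of blinding does not cover a recording procedure that differs by phase, and time stamps do not replace a stated rule.

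**Conclusion.** The point holds as a risk, not as a demonstrated bias. By the text of Section 2.9, an unblinded treating investigator writes AEs into the primary-outcome diary in phase B only, with no stated separation. The exposure is at most 0.8 days per 28 days for each entry miscounted as a headache day, and zero if none is. Any such error would dilute an apparent benefit, so it could not by itself create one. The figure of 4.0 per 28 days is an arithmetical ceiling and should not be read as an expected effect.

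The second part rests on the schedule alone: non-specific reactions have no within-patient comparator, because no AE enquiry is described before treatment. That these symptoms overlap with migraine is plausible, but the document does not state it, and the background rate is unknown. Needle-specific events are unaffected. The change is worth making because it is cheap, but the point is not fatal to the trial.

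**What to change.** In Section 2.9, record AEs on a separate form with date, relation to session and outcome. Leave diary entries to the participant in both phases, and state that an AE record is not counted as a headache day. A headache that the participant enters would still be counted by the same rule in A and B.

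Add one short question on tiredness, drowsiness, dizziness and tingling to the weekly diary report, worded identically in both phases. Report weeks with symptoms in A against B for each participant, descriptively.

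The cost is one form, 4 to 7 extra baseline answers per participant according to tier, and 5 in phase B. The weekly reports are already scheduled, so no visits or staff are added.

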## 2. Methods

### 2.1. Study Design

This study protocol and subsequent experiment will follow the Single-Case Reporting Guideline in Behavioral Interventions (SCRIBE) 2016 [35]. This project was approved by the Mass General Brigham Institutional Review Board (protocol #2023P000931) and is registered with ClinicalTrials.gov (NCT05893914). This study will implement a single-case, non-concurrent, multiple-baseline experimental design, using an AB design (A = baseline, B = treatment). To strengthen the internal validity of this experiment, participants will be randomly assigned to one of four baseline tiers, leading to four potentially different start dates for each participant in the intervention phase. The first tier will include 4 weeks (28 days) of baseline measurements (phase A), followed by 5 weeks of treatment and symptom monitoring (phase B); the second tier will include 5 weeks (35 days) of baseline measurements (phase A), followed by 5 weeks of treatment and symptom monitoring (phase B); the third tier will include 6 weeks (42 days) of baseline measurements, followed by 5 weeks of treatment and symptom monitoring (phase B); and the fourth tier will include 7 weeks (49 days) of baseline measurements, followed by 5 weeks for treatment and symptom monitoring (Figure 1). According to the International Headache Society, a 28-day minimum prospective baseline period using a headache diary is recommended to establish the attack frequency in a study of chronic migraine [36]. The length of the baseline and follow-up periods were chosen to ensure a minimum of 4 to 5 assessments per participant per phase, as recommended for the analyses of SCEDs [31]. In total, the duration of the study will be 9–12 weeks depending on the baseline assignment. In the intervention phase (phase B), all participants will receive one intervention session per week, over five weeks.

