### 2.3. Participant Selection

#### 2.3.1. Inclusion Criteria

To be eligible, patients must be adults between the ages of 18 and 65 years. Participants will be included if they have at least a 6-month history of headaches consistent with a diagnosis of chronic migraine headache according to International Headache Society (IHS) criteria [1], as determined by a neurologist. That is, headaches occurring on 15 or more days/month for more than three months, which, on at least eight days/month, have the features of a migraine headache. In addition, participants must have active TrPs ipsilateral to the side of headache and reproducing headache symptoms upon stimulation within the distribution of headache in at least 2 of the following posterior cervical muscles: splenius capitis, splenius cervicis, semispinalis capitis/cervicis, cervical multifidi, and obliquus capitis inferior.

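### The stop rule in 2.9 compares a run of consecutive headache days with a weekly average count, so unchanged chronic migraine can prompt advice to leave the study before the 6th visit

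*Protocol article*

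**What the plan says.** Section 2.9 gives two triggers. One is "an increase in the average headache pain intensity of more than two points on the NPRS following the first week of treatment", which has a margin and a time anchor. The other applies "if a subject reports an increased number of consecutive headache days above their reported weekly average"; it has no margin and does not refer to the participant's usual run length. In either case, "the principal investigator will consult the patient and recommend discontinuation of the study".

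Three other parts of the protocol bear on this:
- Section 2.3.1 requires "headaches occurring on 15 or more days/month for more than three months".
- Section 2.6.1 states: "The primary end point for this study is the 6th, and final, visit at the end of the intervention phase". It also states: "Headache diary reports will be sent to the principal investigator each week during the baseline and intervention periods of the study".
- Section 2.1 chose the phase lengths "to ensure a minimum of 4 to 5 assessments per participant per phase, as recommended for the analyses of SCEDs".

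Nothing elsewhere in the protocol limits or explains the second trigger.

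**The concern.** A person with headache on half of all days has an average of 3.5 headache days per week. Four headache days in a row is an ordinary event for that person, yet it exceeds 3.5 and so meets the trigger. The rule therefore separates worsening from the usual course of the disease poorly.

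The advice is to leave the study, not only to stop needling, and it can come before the visit at which the primary end point is assessed. There are four participants, so each one who accepts a false prompt before that visit takes away a quarter of the end point assessments. Someone who leaves at or before the week 3 review has at most three weekly phase B assessments, below the minimum that section 2.1 aims for. The trigger also uses headache days, the primary outcome variable, so leaving depends on the outcome: phase B is cut off just after a bad run.

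**Working it through.** The protocol gives no trigger rate, so there is no figure to reproduce.

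**Inputs from the protocol.** At least 15 headache days/month (2.3.1); phase B of 35 days (2.1); weekly diary reports and the end point at the 6th visit (2.6.1); four participants (2.2).

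**Assumptions, not in the protocol.** Days are independent, the daily rate p is unchanged from baseline, and rates run from 15 to 26 days per 28.

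**Threshold.** The weekly mean is 7p, and the shortest triggering run is k = floor(7p) + 1.
- 15/30: 7 × 0.5 = 3.5, so k = 4.
- 15/28: 3.75, so k = 4.
- 16/28: exactly 4, so k = 5.
- 26/28: 6.5, so k = 7.

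**Window.** Reports are reviewed weekly. A run first completed in days 29 to 35 is seen at about the 6th visit and costs no end point. The window that matters is 28 days.

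**Formula.** Let a(n) be the chance of no run of k or more in n days. Then a(n) = 1 for n < k, a(k) = 1 − p^k, and for n > k, a(n) = a(n−1) − (1−p) p^k a(n−k−1). The chance of a trigger is 1 − a(n).

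Worked for 15/30 over one week: p^k = 0.0625 and (1−p)p^k = 0.03125. So a(4) = 0.9375, a(5) = 0.90625, a(6) = 0.875, a(7) = 0.84375, and the chance of a trigger is 15.6%.

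| Rate | k | one check after week 1 (7 days) | by day 21 | by day 28 | by day 35 |
|---|---|---|---|---|---|
| 15/30 | 4 | 16% | 50% | 61% | 70% |
| 15/28 | 4 | 20% | 59% | 70% | 79% |
| 16/28 | 5 | 11% | 42% | 54% | 63% |
| 20/28 | 6 | 17% | 60% | 73% | 81% |
| 24/28 | 7 | 34% | 85% | 93% | 97% |
| 26/28 | 7 | 60% | 98% | over 99% | over 99% |

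The rates do not rise smoothly because k moves in whole days; 16/28 is the lowest point.

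**At least one of four prompted by day 28, lowest case (16/28):** 1 − (1 − 0.537)^4 = 95%. With one check after week 1: 1 − (1 − 0.113)^4 = 38%.

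**Sensitivity of the 28-day figure.**
- Day-to-day correlation +0.3: 77% at 16/28, 87% at 15/28. Correlation −0.1: 45% and 62%.
- Treatment removes 5 days/28: 13% at 16/28, 24% at 15/28, 67% at 26/28.
- A true rise of 6 days/28 from 15/28: 99%, against 70% with no change.

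**Effect on the analysis if every prompt is accepted at the weekly review and treatment does nothing** (simulation, four baseline weeks):
- The mean per-person phase B rate is about 0.7 to 1.3 days/28 too high.
- Mean NAP is about 0.41 to 0.44 instead of 0.50, and 0.31 to 0.42 in those who stop by week 3.
- The pooled rate over four people shifts by only about 0.2 to 0.4 days/28.

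**The case against.** **The action is advice after a consultation.** This stands. A reader might take the trigger rates as loss rates and infer that most participants will drop out. The protocol does not support that: it gives no acceptance rate, and every bias figure above assumes full acceptance and shrinks as acceptance falls.

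**The window is uncertain.** This stands in part. The phrase about the first week of treatment sits with the pain limb but could govern both limbs, which gives 11% to 60%. Counting runs only within calendar weeks also lowers the figure: at 15/30, 57% over all five weeks against 70% for unrestricted runs. A reader might quote the 35-day rates as loss of the end point; runs that finish in the last week do not cost the 6th visit, so those rates are too high for that purpose. The word increased might be meant relative to the person's usual run, but the stated comparator is the weekly average. A rule whose trigger rate depends this much on the reading needs rewording in any case.

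**The inferential harm is modest.** This stands for the pooled result. The mixed model in section 2.7.2 uses all available points, and the bias runs against treatment, so it cannot create a false benefit. It does not help the individual plots and non-overlap indices, nor can it restore a 6th visit that did not take place.

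**A sensitive safety prompt is defensible in an unblinded exploratory study.** This is a fair argument for a low threshold for consultation. It is not an argument for comparing two different quantities, or for ending data collection.

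**Conclusion.** The point holds as a badly fixed rule that should be amended. The mismatch of quantities is in the text and needs no assumption. Its size does: with independent days and an unchanged rate of 15 to 26 days/28, the trigger is met in time to cost the 6th visit in about 54% to over 99% of participants, or in 11% to 60% if there is one check after week 1. Positive day-to-day correlation raises the 28-day figures and slight negative correlation lowers them.

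The consequence is a possible loss of one of four end point assessments per accepted false prompt, and an individual phase B record biased against treatment. It is not a predicted withdrawal rate, a material bias in the pooled estimate, or a route to a spurious benefit.

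**What to change.** Amend section 2.9 in two ways.

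1. **Compare like with like.** Set headache days in a treatment week against the participant's own baseline weekly mean plus a margin, over a stated window, both chosen by the clinical team. A single bad week can still prompt a consultation. Participants near daily headache have no room to exceed such a margin and need another criterion from the diary, for example intensity or acute medication days; section 2.6.1 already provides that "Headache characteristics, triggers, and medication use will also be recorded in the headache diary".
2. **Change the action.** Recommend that needling stop, not that the participant leave the study. Continue the weekly diary reports to day 35, keep the 6th visit, and mark the stop date on the plots.

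An illustration of the trade-off, not a recommended rule: two treatment weeks in a row, each more than 1 day above the baseline mean. With independent days, a known mean and rates of 15 to 22 days/28, this fires over 35 days in 3% to 26% of unchanged participants and in 65% to 100% after a rise of 6 days/28. From 24 days/28 upwards it can never fire, since a mean of 6 plus 1 already equals 7.

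The cost is a wording change; the diary reports and the 6th visit are already planned. The downsides are that a rule with a margin reacts later and misses some true rises, and that weeks recorded after needling stops dilute the on-treatment effect.
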